**DATES:**

**start:** April 2009

**end:** September 2011

**SUMMARY**

*Plasmodium vivax* is the most widely spread of the four malaria species and the main cause of malaria outside Sub-Sahara Africa. In Central Vietnam, nearly 50% of malaria infections are due to *P.vivax*, causing a heavy morbidity burden for the local population due to the activation (relapse) of dormant liver forms (hypnozoites) weeks or months after the primary infection. The national guideline for the radical cure of *P.vivax* infection was changed in 2007, with an increase of the daily dose of primaquine from 0.25mg/kg to 0.50mg/kg for 10 days (the 3-day concomitant chloroquine regimen (total 25mg/kg) remaining unchanged). The efficacy of this new regimen in preventing short as well as long term relapses has not been evaluated yet. Moreover, the epidemiology and the transmission dynamics of *P.vivax* remains poorly documented due to the lack of reliable tools to distinguish between new infections, recrudescence and relapses. Consequently, as control strategies cannot be adequately adapted to the local epidemiology, *P.vivax* morbidity continues to contribute to the vulnerability of the local populations, mainly ethnic minorities, with poor health and socio economic status. The main objective of this study is to establish a new tool that will assist the National Malaria Control Program to improve control strategies for *P.vivax* in Vietnam. This tool will be based on molecular (microsatellites) and serological (CSP ELISA) techniques and on mathematical modelling, to distinguish between a new infection, and a relapse/recrudescence of *P.vivax*. A cohort of 250 *P.vivax* infected patients will be treated and followed up for 2 years in order to estimate the efficacy of the current treatment guideline in preventing recrudescence and relapses, and determine the incidence of new infections. The development of such a tool is extremely important for the control of *P.vivax* in Vietnam since it will help to understand the epidemiology of *P.vivax* and to test targeted interventions, including new drugs. Eventually, the National Malaria Control Program will be able to adapt its control strategies and monitor the efficacy of the treatment guidelines. This study will be conducted concomitantly to a similar one in the Peruvian Amazon (“sister project”), in order to compare the results and to validate the new tool. In addition, this project will contribute to strengthen the institutional collaboration between NIMPE, Hanoi and ITM, Antwerp with the training of 2 Vietnamese junior scientists (1 Msc and 1 PhD), and to develop a new South-South collaboration between the NIMPE, Hanoi and ITM-AvH, Lima, through simultaneous training of 2 Peruvian students. Exchange of information, experience and expertise on *P.vivax* between the 2 southern institutions is likely to boost new perspectives in R&D in 2 endemic regions facing similar challenges for malaria control.

# BACKGROUND

According to the national control program (NMCP), half of the malaria morbidity and about 90% of its mortality occurs in the 16 forested provinces situated in Central Vietnam (1, 2). In these areas, *Plasmodium vivax* represents about half of all malaria cases (3, 4), and the local populations bear a heavy morbidity burden due to the activation (relapses) of dormant liver forms (hypnozoites) weeks or months after the primary infection. Hypnozoites can be treated with a 2-week course of primaquine as recommended by WHO (5). However, treatment adherence is usually low and self-treatment with inappropriate drugs or inadequate dosage is common as symptoms are often mild. Therefore, Vietnam has recently (2007) doubled the daily dose of Primaquine (from 0.25 to 0.5mg/kg) in its 10-day protocol (6). However, the efficacy of this new regimen in preventing short- and long-term relapses has not yet been formally evaluated. Moreover, the epidemiology of *P.vivax* is poorly documented because the currently available techniques cannot discriminate between relapses/recrudescences and new infections. Therefore, the incidence of new infections and related risk factors cannot be estimated, the current treatment efficacy and the impact of control activities cannot be accurately evaluated and new interventions cannot be tested. This results in a *statu quo* as control strategies cannot be adapted to the local epidemiology, and consequently maintains the vulnerability of local populations, mainly ethnic minorities with poor health and socio-economic status. We propose to set up a new tool that will assist the NMCP in understanding the transmission dynamics of *P.vivax*, in monitoring the treatment efficacy, and in designing and evaluating targeted strategies to control *P.vivax* malaria. This method will combine molecular, serological and epidemiological markers that will be incorporated in a mathematical model to estimate the probability for a given vivax episode to be a new infection. Similar models have already been developed for *P. falciparum* (7) and will be adapted for *P. vivax*. Currently, the best molecular markers for *P.vivax* genotyping are micro-satellites (MS), which are highly polymorphic tandem repeats. However, genotyping alone is not sufficient since a true relapse could have a different genetic pattern from the primary infection (8), due to different parasite clones present in the liver. Thus, recent exposure to an infective mosquito bite needs also to be checked by measuring antibody titres against *P. vivax* circumsporozoite protein (CSP), short-lived (1 month) and specific against sporozoites. This can be done with an existing CSP Enzyme Linked Immunosorbent Assay (ELISA) (9-10). MS markers and CSP-ELISA are currently under development at ITM, Antwerp.

# OBJECTIVES

## Main objective

To improve malaria control strategies in Central Vietnam by characterizing *P.vivax* epidemiology and identify potential targets for intervention.

## Specific objectives

1. To establish in a defined cohort of *P.vivax* patients, the short and long term efficacy of the new national treatment guideline in preventing recrudescences and relapses;
2. To characterize *P.vivax* transmission dynamics and indentify vulnerable groups among the local population (in a representative sample of the study population);
3. To set up a new tool, based on genotyping, serology and modelling able to accurately distinguish between *P.vivax* new infections and relapses.

# MATERIALS & METHODS

## Study site and population

The study will be carried out in the 2 neighbouring communes of Tra Leng and Tra Don situated in Nam Tra My district, Quang Nam Province, Central Vietnam, where several malaria outbreaks have occurred in the past, and currently with most *P.vivax* casesin the province (11). The latter come mostly from Villages 1, 2 and 3 in Tra leng and from Village 3 in Tra Don commune. The commune health centre (CHC) of Tra leng is situated in Village 1, which is contiguous to Village 3, while Village 2 is situated at 2h walking distance through the forest on the top of a mountain. Village 4 is located even further (4h walking distance) and will be included in the study area in a second phase (March 2010) in order to increase the recruitment rate. The area is still densely forested and mountainous, a perfect site for *Anopheles dirus*, though the main vector species identified in entomological collections by the Provincial Malaria Station (PMS) is *An.minimus A,* together with other species such as *An.vagus, An.aconitus,* or *An.philippinensis* (12).

The climate is sub-humid with an average annual rainfall of about 1,200-2,000mm and two seasons: the dry season from December to April, and rainy season from May to November. Malaria transmission is perennial with 2 peaks: the first at the beginning of the rain (March-May), and the second between August and October. Annual reports from the national program show that about 40 to 45% of the malaria cases are due to *P.vivax* and all age groups are infected. The 2 communes totalled up to 400 and 300 cases, respectively in 2005 and 2006, with a total annual incidence of about 150 *P.vivax* cases/1000 populations. In 2007, the incidence dropped to 153 cases, and in 2008 only 106 cases were detected. Despite the decreasing incidence, more cases can probably be found by systematic screening.

The population of the 4 initial study villages comprises about 2,100 inhabitants (370 households), 85% belonging to the M’nong ethnic minority and 15% to the Cadong, clustered into small hamlets of 15-20 houses (February 2009 Census). The census of Village 4 will be carried out in March 2010. People are usually very poor, living in bamboo or wooden houses on the slope of the mountains. Most people practice subsistence agriculture, cultivating maize, manioc and rice in their forest fields and for the richer ones planting cinnamon trees. Most people rear goats and pigs and for those who can afford it cattle and buffaloes. ITN use is not very popular among the M’nong as they fear burning them because they usually sleep near the fire. Each commune has a CHC staffed by a few nurses, one microscopist (3-month training) and a midwife. They supervise the hamlet health workers (usually one per hamlet) who are involved in health education and prevention activities. They are also trained to take blood slides from febrile patients and bring them to the CHC for reading. Whenever a slide is found positive for malaria parasites, the patient is referred to the CHC for treatment. Quality control of the microscopic examination is done at district and at provincial level.

## Study design

This is a prospective longitudinal study of a cohort of *P.vivax* infected patients initially treated with the radical cure regimen following national guidelines and followed-up monthly for 2 years.

### Cohort recruitment

Vivax infected patients will be recruited during the initial screening/survey and/or during one year of the passive case detection (PCD) continued in each study village during the whole cohort follow-up.

Initially, the recruitment period was foreseen from April 2009 to April 2010. Since only 117 *P.vivax* patients could be recruited by February 2010, it was decided to extend the recruitment until December 2010 in order to reach the target number of 250 patients included.

*Inclusion criteria*

- Age ≥ 3years
- *P.vivax* mono-infection (asexual stages);
- Resident in the study villages;
- Written informed consent (parent/guardian for minors);

*Exclusion criteria*

- General danger signs with severe or complicated malaria according to WHO definitions (Annex B to this protocol);
- Pregnancy (rapid test positive or pregnancy clinically confirmed) or breastfeeding;
- Known G6PD deficiency (or history of “black urine” after previous primaquine treatment), or any history of side effects to the study drug;
- Documented radical cure with Primaquine (10 days at 0.5mg/kg) within one month prior to inclusion;
- Underlying chronic diseases (TB, lupus, diabetes, rheumatoid arthritis, etc);
- Concomitant infectious disease requiring antibiotic treatment;
- Severe malnutrition;
- Patients with neuro-psychiatric disorders or previous history (epilepsy, dementia, ..)

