### Sample size calculation

Two different sample sizes were calculated: one for the estimation of *P.vivax* failure rate for chloroquine (28-day follow-up) and for Primaquine (2-year follow-up) in a cohort of *P.vivax* patients initially treated with the current radical cure regimen, and the second for the population survey on *P.vivax* prevalence (in a random sample of the study population).

- ***P.vivax population survey***

A total2,100 individuals at risk of malaria were estimated in the 4 study communes (census February 2009). According to the provincial malaria station (PMS) data on surveys carried out in April-May, the overall parasite rate was around 16% (ranging from 5 to 39% across hamlets) and the prevalence of *P.vivax* at 9%. In order to detect a minimal prevalence of 9% with 3% precision and at 5% significance level, a total of 300 individuals is needed for the survey (“CSample” command/EpiInfo6). After “finite population correction” and adding 10% security margin, a final sample size of 300 individuals would be sufficient. Since there are a total of about 370 households and in order to simplify sampling procedures, one individual in each house visited for the screening will be randomly selected to participate in the survey. This will be done by randomly choosing from the census file. The selected individual will be asked oral informed consent before starting in-depth interview.

- ***P.vivax cohort***

Between 2003 and 2007, *P. vivax* late parasitological failure to CQ was monitored in several Central Vietnam provinces and ranged from 0% to 5.7% (13). Therefore, to detect a failure rate as low as 5% with a 3% precision at 5% significance level, a minimum of 185 individuals are needed (“CSample” command/EpiInfo6). Assuming a maximum drop out rate of 10% during the first 28 days, a total of 204 cases will be necessary. For the estimation of a similar PQ failure rate after 2 years of follow-up, a total of 230 patients should be included with a maximum of 20% drop out during the 2-year follow-up.

By including 250 vivax patients in the cohort, and assuming a maximum drop out rate of 20% during the 2-year follow-up, we can expect to get a final database of 200 patients with a complete follow-up (i.e. 31 successive sampling results) for the modelling of *P.vivax* new infections/relapses.

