### *P.vivax* patients’ treatment & cohort follow-up

Patients identified during either the initial screening/survey or during PCD and fulfilling all the inclusion criteria (all present) and exclusion (all absent) criteria will be included in the cohort. They will be treated with a 10-day radical cure regimen of Primaquine, and will be monitored during the first 28 days following standard WHO protocol for *in vivo* antimalaria drugs efficacy studies, then monthly checked for malaria symptoms and parasites for 23 months.

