**Table 2. Patients’ follow-up schedule during the first 28 days**

|  | **D0** | **D1** | **D2** | **D3** | **D4** | **D5** | **D6** | **D7** | **D8** | **D9** | **D14** | **D21** | **D28** | **Dx** | **M*** | **Mx** |
| --- | --- | --- | --- | --- | --- | --- | --- | --- | --- | --- | --- | --- | --- | --- | --- | --- |
| **PROCEDURES** |  |  |  |  |  |  |  |  |  |  |  |  |  |  |  |  |
| Clinical examination | **X** | **X** | **X** | **X** | **X** | **X** | **X** | **X** | **X** | **X** | **X** | **X** | **X** | **X** | **X** | **X** |
| Assess adverse event | **X** | **X** | **X** | **X** | **X** | **X** | **X** | **X** | **X** | **X** | **X** | **X** | **X** | **X** |  |  |
| Body temperature | **X** | **X** | **X** | **X** | **X** | **X** | **X** | **X** | **X** | **X** | **X** | **X** | **X** | **X** | **X** | **X** |
| Thick+thin film | **X** | **X** | **X** | **X** |  |  |  | **X** |  |  | **X** | **X** | **X** | **X** | **X** | **X** |
| Filter paper 2 spots  (ELISA & PCR) | **X** |  | **X** | **X** |  |  |  | **X** |  |  | **X** | **X** | **X** | **X** | **X** | **X** |
| Hemoglobin | **X** |  |  |  |  |  |  |  |  |  | **X** |  | **X** |  |  |  |
| Filter paper CQ  (100µl capillary) | **X** |  |  |  |  |  |  | **X** |  |  |  |  | **X** | **X** |  |  |
| Direct observation of treatment | **X** | **X** | **X** | **X** | **X** | **X** | **X** | **X** | **X** | **X** |  |  |  |  |  |  |

**Dx**: Any other day if the patient feels febrile or unwell

**M***: monthly visits by HHW from 2nd to 24th month

**Mx:** unscheduled monthly visit if patient feels sick

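### The stated study end of September 2011 cannot hold 24 months of follow-up for patients recruited to December 2010, so the 200 complete series promised are capped at 117 before drop-out

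*Protocol*

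**What the plan says.** - **Front matter, Dates:** the study starts in April 2009 and ends in "September 2011".
- **3.2.1 Cohort recruitment:** "Initially, the recruitment period was foreseen from April 2009 to April 2010". The window was later lengthened: "it was decided to extend the recruitment until December 2010 in order to reach the target number of 250 patients included". The reason given is slow accrual, with 117 patients enrolled by February 2010.
- **3.2 Study design:** patients are "followed-up monthly for 2 years".
- **3.3.3 Treatment and cohort follow-up:** after the 28-day phase patients are "then monthly checked for malaria symptoms and parasites for 23 months". The footnote to Table 2 agrees: "monthly visits by HHW from 2nd to 24th month".
- **3.2.6 Sample size calculation:** from 250 enrolled with at most 20% drop-out, "we can expect to get a final database of 200 patients with a complete follow-up (i.e. 31 successive sampling results"). These series feed the model that separates new infections from relapses. The same section sets 185 patients as the minimum for a 5% failure rate with 3% precision, and raises this to 230 for the primaquine failure rate at 2 years.

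No section moves the end date, shortens follow-up for late entrants, or says that follow-up will be cut off at a calendar date.

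**The concern.** Recruitment was lengthened, but neither the end date nor the expected number of complete series changed with it. A patient who enters in December 2010 and is followed for 24 months finishes in December 2012, 15 months after the stated end.

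Two things depend on complete follow-up. One is the modelling database, which 3.2.6 describes as 200 patients with all 31 samplings. The other is the 2-year precision of 5% ± 3%, which the same section bases on 185 patients left after drop-out. If the stated dates govern, neither can be had. The patients with full series would also all be early entrants. None would come from Village 4, which joins in March 2010 and can have at most 19 months.

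**Working it through.** **Inputs.** Start April 2009 and end September 2011 (Dates); 117 enrolled by February 2010, target 250, recruitment to December 2010 (3.2.1); 24 months per patient (3.2, 3.3.3, Table 2); drop-out 20%, failure rate 5%, precision 3% (3.2.6); population about 2,100 (3.1).

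**1. The plan's own figures.**
- n₀ = 1.96² × 0.05 × 0.95 / 0.03² = 202.7. With a finite population correction for 2,100: 202.7 / (1 + 202.7/2,100) = 184.9, so 185. This matches.
- 185 / 0.8 = 231.25, so 232 against the stated 230. The gap is immaterial.
- 250 × 0.8 = 200. This matches.
- Blood slides on days 0, 1, 2, 3, 7, 14, 21 and 28 make 8; months 2 to 24 make 23; 8 + 23 = 31. This matches.

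The 200 therefore allows for drop-out only, and not for follow-up cut short by the calendar.

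**2. Calendar.** From 1 April 2009 to 30 September 2011 is 30 months, the most generous reading. Reaching 24 months requires entry in the first 30 − 24 = 6 months, by the end of September 2009.

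| Entry | Longest possible follow-up |
| --- | --- |
| End September 2009 | 24 months |
| End February 2010 | 30 − 11 = 19 months |
| December 2010 | 30 − 20 = 10 to 30 − 21 = 9 months |

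A December 2010 entrant with 9 months would have 8 + 8 = 16 of the 31 samplings, or 17 with 10 months.

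**3. Upper bound, without any accrual assumption.** The remaining 250 − 117 = 133 patients all enter too late. Those enrolled by end September 2009 are a subset of the 117. Completers are therefore at most 117 before drop-out and 117 × 0.8 = 93.6, about 94, after it. The like-for-like comparison with the stated 200 is 94, which is 47% of it. Both 117 and 94 fall below 185.

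**4. Precision at a 5% rate.** Half-width = 1.96 × √(0.05 × 0.95 / n).
- n = 200: 3.0%
- n = 117: 3.9%
- n = 94: 4.4%

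With a finite population correction the last two become 3.8% and 4.3%.

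**5. If accrual was even (an assumption).** Take the 117 as spread over 10 or 11 months, with 5 or 6 of those months falling before the cut-off.
- Lowest: 117 × 5/11 = 53; after 20% drop-out, 43.
- Highest: 117 × 6/10 = 70; after 20% drop-out, 56.

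**6. Person-time left, before drop-out, again with even accrual in each period.**
- First 117 patients over 11 months: 117 × (6/11 × 24 + 5/11 × 21.5) = 2,675 patient-months.
- Next 133 patients over 10 months, mean follow-up 30 − 16 = 14 months: 133 × 14 = 1,862 patient-months.
- Total 4,537 of 250 × 24 = 6,000, or about 76%.

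**The case against.** The strongest reply is that the end date is a bare label in the front matter, and every substantive section asks for 2 years per patient. Even the first-planned close of April 2010 did not fit September 2011, since April 2010 entrants would have had only 17 to 18 months. The likeliest explanation may be a date that was never brought up to date, in which case 200 is attainable once it is corrected. This is fair, and it makes the repair easy. It does not remove the contradiction: the recruitment text is current, and nothing in the document says which statement governs.

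Three stronger readings are tempting, and the document does not support them.

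- **That 2-year efficacy would be overstated, because unobserved months would count as free of recurrence.** No section plans a crude 2-year proportion over all 250. Section 3.2.5 defines the second primary endpoint as the incidence of recurrent infection after day 28, which can be estimated with unequal follow-up. Details of the estimator may properly sit in an analysis plan that is not shown.
- **That the dates deliver only some 50 to 65 completers.** They deliver only an upper bound. Any figure of that size rests on even accrual, which is doubtful because recruitment opens with screening of the whole population. At the 9% *P. vivax* prevalence in 3.2.6, 2,100 people would hold about 189 infections before eligibility and consent. Entry may well have been front-loaded, though still within the 117.
- **That both primary endpoints fail.** December 2010 entrants reach day 28 by January 2011, so treatment failure at day 28 is untouched. Late entrants still add censored person-time to recurrence incidence.

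**Conclusion.** The contradiction stands. With the stated end date, the 200 complete series and the 185 needed for 5% ± 3% at 2 years cannot be reached. The ceiling is 117 before drop-out and about 94 after 20%, which gives half-widths of about 3.9% and 4.4%.

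The ceiling of 117 rests only on the stated dates, the February 2010 count and 24 months per patient; the 94 adds the protocol's own drop-out rate. The true number is whatever was enrolled by the end of September 2009, which the protocol does not report. The 76% of person-time holds only under even accrual, and earlier entry would raise it. The damage is confined to complete 2-year follow-up: the modelling database and the 2-year precision statement.

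**What to change.** Reconcile the dates, section 3.2.1 and section 3.2.6 by amendment, in one of two ways.

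1. **Move the study end to December 2012.** Full follow-up then fits for every entrant, and the 200 stands subject to the assumed drop-out. The cost is up to 15 more months of monthly visits and sampling.
2. **Keep September 2011.** State that follow-up is administratively censored then, and analyse recurrence by time-to-event or person-time methods. Replace the 200 completers and the 2-year precision with figures based on the actual number enrolled by end September 2009, which the sponsor knows. That number is at most 117 before and about 94 after drop-out; 53 to 70 before and 43 to 56 after would apply only if accrual was even. This has no field cost, but the modelling plan must then accept series shorter than 31 samplings.

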### Loss to follow-up

Loss to follow up occurs when, despite all reasonable effort, an enrolled patient that does not attend the scheduled visits cannot be found. No treatment outcome will be assigned to these patients during the 28-day follow-up. These patients will be classified as lost to follow-up. Patients who are lost to follow-up, but who subsequently come back to the study site before the end of the 28-day follow-up (or the end of the 2-year follow-up), will not be turned away and will also be encouraged as much as possible to return into the follow-up. The reason and location (geographical) of the absence must be written in the follow-up forms Annex 7 or Annex8, accordingly). These patients will be classified as “temporarily lost”.

Every effort must be taken to trace the patients for their follow-up visits with the help of the HHW (and community members) during the entire follow-up period.

